| Prior medication review |  | X | X | X | X | X | X | X | X | X | X | X | X |  | X |
| Tests to be carried out at subjects’ homes | | |  |  |  |  |  |  |  |  |  |  |  |  |  |
| Instructions on the portable test devices / ePRO | X |  |  |  |  |  |  |  |  |  |  |  |  |  |  |
| Test using the portable devices and ePRO input (at patients’ home) |  |  |  |  |  |  |  |  |  |  |  |  |  |  |  |
| Collection of data from portable devices and ePRO |  | X | X | X | X | X | X | X | X | X | X | X | X | X | X |
| Collection of the portable devices and ePRO |  | X^3^ |  |  |  |  |  |  |  |  |  |  |  | X | X |
| In-hospital tests and observation | |  |  |  |  |  |  |  |  |  |  |  |  |  |  |
| Medical interview on dizziness | X | X | X | X | X | X | X | X | X | X | X | X | X | X | X |
| Thoracic X-ray | X |  |  |  |  |  |  |  |  |  |  |  |  |  |  |
| Pure-tone audiometry | X | X |  | X | X | X |  | X | X | X | X | X | X | X | X |
| Auditory brainstem response | X |  |  |  | X |  |  |  |  |  |  |  | X |  | X |
| Posturography | X | X |  | X | X | X |  | X | X | X | X | X | X | X | X |
| Carolic and c-VEMP tests | X |  |  |  |  | X |  |  |  | X |  |  | X |  | X |
| Speech audiometry | X |  |  |  | X |  |  |  |  |  |  |  | X | X | X |
| Thyroid ultrasound | X |  |  |  |  | X |  |  |  |  |  |  | X |  | X |
| MRI (optional)^4^ |  |  |  |  |  | X^5^ |  |  |  |  |  |  | X^5^ |  | X^5^ |
| Cytology test (optional) |  |  |  |  |  | X |  |  |  |  |  |  | X |  | X |
| Blood collection for generation of iPS cells (optional)^6^ |  |  |  |  |  |  |  |  |  |  |  |  |  |  |  |
| Blood collection for measurement of drug concentration in blood |  |  |  |  |  | X | X | X | X | X | X | X | X |  | X |
| Clinical laboratory tests (blood sampling and urinalysis)^7^ | X | X |  | X |  | X | X | X | X |  | X |  | X | X | X |
| Physical findings (height and weight) | X | X |  |  |  | X |  |  |  |  |  |  | X |  | X |
| Blood pressure, pulse, and temperature | X | X | X | X | X | X | X | X | X | X | X | X | X |  | X |

^1^ The initial administration of investigational products in Phase II for respective subjects shall not be scheduled for the same day.

^2^ The interval between V5 and V6 and between V6 and V7 should be 10 days or more.

^3^ Applies when disqualified by the eligibility judgment.

^4^ An image taken at an external institution may be used if the date of imaging falls within the allowable window and is obtained with the consent of the patient.

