^5^ The allowable visit windows are to be four weeks before V5, four weeks after V12, and four weeks after discontinuation. This examination may be performed on an alternative date as an exception.

^6^ If blood was collected in the past for generation of iPS cells, and consent for its use for the clinical trial has been obtained, blood collection need not be newly performed.

^7^ Hematocrit, serum triglyceride, viral tests, thyroid autoantibody tests, pregnancy test are performed at V0 only. Thyroid hormone tests are performed at V1, V5, V12, and discontinuation only.

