### Period for Administering the Investigational Products

NPC-12T tablets (active substance): 178 days maximum

NPC-12T tablets (placebo): 259 days maximum

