## Study Population

Outpatients with fluctuating hearing diagnosed as PDS in *SLC26A4* genetic testing are eligible to participate if all of the inclusion criteria described below are met, and if none of the exclusion criteria below are met.

[Inclusion Criteria]

1) Aged at least seven and below fifty years at the time of consent

2) Confirmed PDS-positive by genetic testing such as Sanger Sequencing

3) Report of subjective symptoms of fluctuating hearing disorder in a medical interview for case registration

4) Subjective symptoms of episodes of hearing loss and/or dizziness/vertigo within one year prior to the case registration

5) Had undergone inner-ear function testing at least three times, including standard pure-tone audiometry, performed with an interval of one day or longer, within six months prior to the case registration

6) Voluntary informed consent in writing obtainable from the patient or the patient’s legally acceptable representative

[Rationale]

1) To allow participation of patients of a wide range of ages, in consideration of patient demographics

2) through 5) To select patients who are considered to be appropriate for evaluation of investigational product efficacy

6) To ensure ethical conduct of the clinical trial

[Exclusion Criteria]

1) Prior use of molecular targeted drugs related to mTOR pathway, such as sirolimus, other mTOR inhibitors (e.g., everolimus) and tyrosine kinase (e.g., bevacizumab, sorafenib)

2) History of hypersensitivity to sirolimus, including sirolimus derivatives, and its additive agents

3) HBs antigen-positive, HBs antibody-positive, HBc antibody-positive, or active hepatitis C (HCV antibody-positive patients with inactive hepatitis and with normal-range values of liver function do not apply.)

HBs antigen-positive patients for which the cause is presumed to be due to vaccination against hepatitis B may participate in this clinical trial.

4) Severe blood abnormalities or hepatic dysfunction that demonstrate conditions shown below.

| Items | Value |
| --- | --- |
| AST or ALT | 100 IU/L or higher |
| Hematocrits | below 30% |
| Platelet count | below 80,000/mm^3^ |
| Absolute neutrophil count | below 1,000/mm^3^ |
| Total white blood cell count | below 3,000/mm^3^ |

5) Patients with poorly controlled dyslipidemia

Serum triglyceride of 500 mg/dL or higher or LDL cholesterol level of 190 mg/dL or higher despite being under treatment for dyslipidemia.

6) Severe renal impairment

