Estimated glomerular filtration rate (eGFR) lower than 30 mL/min/1.73 m^2^

7) Immunodeficiency such as HIV or primary immunodeficiency

8) Inability to take investigational products in tablet form, or gastrointestinal dysfunction with risks of malabsorption of sirolimus

9) History of having surgery within eight weeks prior to the registration (any surgery that requires invasion of the body or suture with three or more stitches, including biopsy)

10) Female patients who are pregnant, potentially pregnant, or breastfeeding. Male or female patients who decline to consent to contraception during the trial

Contraceptive methods: Combination of condoms and spermicide; combination of condoms and diaphragms with spermicide; oral contraceptive; intrauterine contraceptive device; or other methods

11) Need to take medications that influence CYP3A4 activation after the administration of investigational products

12) Pulmonary interstitial opacity

13) Diagnosis by the attending physician during the screening phase or from previous observations from hearing tests that the hearing loss is fixed rather than fluctuating

14) Participation in other clinical research and/or trials within six months prior to the date of consent, with the exception of Analysis of Diseases in Otorhinolaryngology Using iPS Cells (approval No. 20140172)

15) Other conditions that the principal investigator or subinvestigator deems inappropriate

[Rationale]

1) through 7), 9) through 12), and 15) To ensure patients’ safety and to assess safety appropriately

8) The situation disturbs prediction of pharmacokinetics of the investigational products.

13) and 14) These may influence analysis of the investigational products.

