# Endpoints

[Primary Endpoints]

Safety and tolerability:

1) Adverse events (nature, frequency and severity)

2) Side effects (nature, frequency and severity)

3) Clinical laboratory tests

4) Vital signs (blood pressure, pulse, and temperature)

[Secondary Endpoints]

Efficacy:

1) Frequency of hearing loss episodes (number of occurrences/year)

2) Highest measurement of auditory threshold shift at a hearing loss episode (dB)

3) Frequency of dizzy spells (number of occurrences/year)

4) Maximum amplitude (°/sec) and maximum frequency (cycle/sec) of nystagmus during a hearing loss episode

5) Percentage of cases in which increase in hearing threshold was observed during remission in the observation period (comparison of measurements at the end of Phase I and the end of Phase II)

6) Improvement in hearing threshold during remission

7) Shorter duration of hearing loss episodes

8) Alleviation of symptoms of dizziness/vertigo

Changes in total scores of the Dizziness Handicap Inventory from Phase I to Phase II

9) Percentage of cases in which equilibrium exacerbated during remission in the observation period (comparison of measurements at the end of Phase I and the end of Phase II)

[Exploratory Endpoints]

1) Reduction in endolymphatic hydrops (MRI findings)

2) Inhibition of goiter or thyroid enlargement

3) Cell biological changes in thyrocytes detected by cytology tests

4) Comparison of results of in vitro efficacy evaluation of inner ear cells derived from PDS-specific iPS cells and of clinical evaluation

5) Deviation from threshold value for frequency of abnormalities of auditory brain stem responses and for pure-tone audiometry

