If the prescription schedule specifies reduction, the unblinded doctor will instruct the principal investigator or subinvestigator regarding dosage reduction for NPC-12T placebo. The dosage level will be lowered by one tier at a time. The reduced dosage must be no lower than one 1-mg tablet every three days, administered orally. If further reduction is required, administration of the investigational products will be discontinued.

If the principal investigator or subinvestigator determines further reduction is required, administration of the investigational products will be discontinued.

The unblinded doctor will provide instructions to the principal investigator or subinvestigator on prescription in accordance with the specified dosage change in the prescription schedule. The decision by the principal investigator or subinvestigator on permission for dosage increase and reduction shall take precedence over the specification in the prescription schedule, i.e., if the principal investigator or subinvestigator specifies reduction, and the prescription schedule states increase, reduction should be adopted.

[Acceptable change in dosage]

The amounts of investigational products to be administered can be increased or decreased to one of the following dosages:

A. Two 1-mg tablets, once per day, administered orally

B. One 1-mg tablet, once per day, administered orally

C. One 1-mg tablet, once every other day, administered orally

D. One 1-mg tablet, once every three days, administered orally

[Dosage reduction or increase]

When dosage is to be increased, the dosage level should be raised by one tier at a time: Subjects weighing 40 kg or over will follow the change from B to A. Subjects weighing below 40 kg will follow the change from C to B to A.

When dosage is to be reduced, the dosage level should be lowered by one tier at a time, from A to B to C to D. If the current level for a subject is B, for example, C will be applied in the next reduction. If further reduction below D is required, administration of the investigational products to the subject will be discontinued.

[Suspension or reduction of administration of investigational products due to adverse events]

・Unacceptable adverse events or exacerbation considering the safety of the subject

・Unacceptable abnormal observations in clinical tests considering the safety of the subject

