### Laboratory Tests

The principal investigator or subinvestigator will perform the following laboratory tests during the screening phase (V0), Phase I (V1 and V3), Phase II (V5, V6, V7, V8, and V12), follow-up observations (V13), and at discontinuation, and record the results on the electronic case report forms.

[Laboratory test items]

| Tests | Variables |
| --- | --- |
| Hematological tests | red blood cell count, hemoglobin, reticulocyte count, white blood cell count, platelet count, lymphocyte count, neutrophil count, and hematocrit (V0 only) |
| Blood biochemical tests | creatinine, ALP (Changes in the level of ALP will be analyzed as a blood marker), total bilirubin, AST, LDH, ALT, BUN, albumin, CRP, total cholesterol, LDL-cholesterol, uric acid, Na, K, Ca, P, Cl, fasting blood glucose, and serum triglyceride (V0 only) |
| Thyroid hormone tests | FT3, FT4, and TSH (all of these are performed at V1, V5, V12, and discontinuation only) |
| Urinalysis | pH, sugar, protein, and occult blood in urine |
| Viral test | HBs antigen, HBs antibody, HBc antibody, HCV antibody, and HIV antibody (all of these will be performed at V0 only) |
| Thyroid autoantibody tests | TgAb, TPOAb, and TRAb (all of these will be performed at V0 only) |
| Pregnancy test | hCG urine (V0 only) |

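### Serum triglyceride is measured once, at V0, about 14 weeks before sirolimus can first be given, and never on treatment, although LDL from the same safety exclusion is followed.

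*Protocol*

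**What the plan says.** **Triglyceride schedule.** Protocol section 14.7.3 (Laboratory Tests) lists "fasting blood glucose, and serum triglyceride (V0 only" at the end of the biochemistry panel. Footnote 7 under the schedule table in the Protocol Summary, repeated under Table 1, reads "Hematocrit, serum triglyceride, viral tests, thyroid autoantibody tests, pregnancy test are performed at V0 only". The footnote names triglyceride but not glucose, so the limit applies to triglyceride and leaves fasting glucose in the repeated panel. No section schedules a later triglyceride value.

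**LDL schedule.** LDL and total cholesterol are in the same panel without a visit limit. They follow the general laboratory visits: V0, V1, V3, V5, V6, V7, V8, V12, V13 and discontinuation. The table row "Clinical laboratory tests (blood sampling and urinalysis)^7" also marks V10, which the text of 14.7.3 omits.

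**Treatment.** All subjects take placebo in Phase I. Sirolimus or placebo starts at V5, week 12. The exposure limit is given as "NPC-12T tablets (active substance): 178 days maximum".

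**Safety role.** Exclusion criterion 5 (Study Population) is "Serum triglyceride of 500 mg/dL or higher or LDL cholesterol level of 190 mg/dL or higher despite being under treatment for dyslipidemia". The rationale given for criteria 1 to 7 is patients' "safety and to assess safety appropriately". The primary endpoints include "3) Clinical laboratory tests". Under Administration of Investigational Products, one ground for suspending or reducing dosing is "Unacceptable abnormal observations in clinical tests considering the safety of the subject". Section 14.10.2 has changes in clinical test results since before administration judged for clinical significance, and section 17.4.2 plans summaries of change with 95% confidence intervals by arm.

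**The concern.** Criterion 5 joins the two lipids with an *or*: either one alone excludes a subject, on safety grounds. The protocol therefore does not let LDL stand in for triglyceride at entry. Once sirolimus starts, it follows LDL and drops triglyceride, and gives no reason.

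Three parts of the safety plan would use triglyceride values if they existed: the judgement of clinically significant laboratory change, the rule for suspending or reducing dose after unacceptable test results, and the summaries of change by arm. As scheduled, triglyceride can inform none of them. A rise would come to light only through unscheduled testing, which nothing in the protocol prompts and which could not support a comparison between arms.

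The stake is a gap in a primary safety measure, in a trial whose stated purpose includes exploring the safety of sirolimus in this disease. The argument does not assume that sirolimus raises triglyceride, since the protocol does not say so. It rests on the unequal handling of two lipids that the protocol treats as separate safety thresholds.

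**Working it through.** **Inputs, from the schedule tables and the sample size section.** D1 is taken as day 0.

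| Visit | Nominal day | Window | Range |
|---|---|---|---|
| V0 | -14 | ±7 | -21 to -7 |
| V5 | 84 | ±3 | 81 to 87 |
| V12 | 252 | ±7 | 245 to 259 |

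Planned subjects: 12 sirolimus, 4 placebo.

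**1. Reproduce the protocol's own figures.** Longest sirolimus period = latest V12 − earliest V5 = 259 − 81 = 178 days. Longest placebo period = latest V12 − D1 = 259 days. Both match the stated maxima, which confirms V5 as the first possible sirolimus dose.

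**2. Gap from the only triglyceride value to first possible sirolimus.**
- Nominal: 84 − (−14) = 98 days = 14.0 weeks.
- Shortest: 81 − (−7) = 88 days = 12.6 weeks.
- Longest: 87 − (−21) = 108 days = 15.4 weeks.

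**3. Gap from that value to the end of treatment.**
- Nominal: 252 − (−14) = 266 days = 38 weeks.
- Shortest: 245 − (−7) = 252 days = 36 weeks.
- Longest: 259 − (−21) = 280 days = 40 weeks.

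**4. Planned on-treatment values in the 12 sirolimus subjects, if all complete.**
- LDL by the tables (V6, V7, V8, V10, V12): 5 × 12 = 60.
- LDL by the text of 14.7.3 (no V10): 4 × 12 = 48.
- Triglyceride by either source: 0 × 12 = 0.

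**5. Compare with the other laboratory exclusions that carry a numeric limit (criteria 4 to 6).**

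| Exclusion analyte | Followed after V0? |
|---|---|
| AST, ALT | Yes |
| Platelets, neutrophils, white cells | Yes |
| LDL | Yes |
| eGFR | Creatinine is repeated |
| Hematocrit | No, but hemoglobin and red cell count are repeated |
| Triglyceride | No, and no close counterpart is repeated |

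Triglyceride is the only one of these with neither a repeat nor a near substitute.

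**The case against.** The strongest reply is that the schedule is deliberate and consistent. Three places state the same rule, and each names triglyceride individually. Using some tests only for eligibility is a pattern in this protocol: hematocrit is V0 only, and so is the chest X-ray behind the interstitial opacity exclusion. Being screened together does not oblige two analytes to be monitored together. Without a stated reason to expect a triglyceride effect, asymmetry alone could look like preference. The rules on dose suspension and laboratory adverse events say how abnormal results are handled, not which analytes must be drawn, so neither is breached. V0 is also a genuine sirolimus-free value, because everyone takes placebo until V5.

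Several of these points stand. There is no internal contradiction. V0 is a remote baseline, not an absent one, and it counts as pre-administration under section 14.10.2, since administration begins at V1. Total cholesterol and LDL give partial cover. Unscheduled tests are not barred. The counts of 60 and 0 measure planned data, not risk to a subject.

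They do not remove the concern. Hematocrit has close repeated counterparts; triglyceride has none. The X-ray precedent shows that screening-only tests exist here, but LDL shows that the protocol did choose to follow a lipid from this very criterion. A rule stated consistently can still be a poor one when following it leaves part of a primary safety measure unobserved at almost no saving.

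**Conclusion.** The concern holds. Serum triglyceride is planned once, 14.0 weeks (12.6 to 15.4) before sirolimus can first be given and 38 weeks (36 to 40) before the end of treatment. There is no value at V5 and none during up to 178 days of sirolimus. The trial will have 60 planned on-treatment LDL values in the sirolimus arm (48 without V10) and no triglyceride values, so the primary laboratory endpoint covers lipids only in part.

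This is a gap in one analyte, not an absence of lipid monitoring, and it does not threaten the trial as a whole. It should be closed because closing it is cheap and because it cannot be repaired later: the visit schedule is set in the protocol, and an analysis plan cannot summarise values that were never measured.

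The counts assume that all 12 sirolimus subjects complete. The conclusion assumes that the limit attaches to triglyceride as footnote 7 states. It needs no assumption about the direction of any drug effect.

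**What to change.** 1. Remove the V0 limit for serum triglyceride in section 14.7.3 and in footnote 7 under both schedule tables.
2. Assay it on the biochemistry samples already planned at V5, V6, V7, V8, V12, V13 and discontinuation, and at V10 as the tables mark. Fasting glucose is in the same repeated panel, so fasting samples are already planned.
3. Use V5 as the pre-sirolimus baseline. Doses are taken at bedtime, so a sample at the V5 clinic visit should precede the first Phase II dose; state this explicitly.
4. Summarise values and changes from V5 by arm with two-sided 95% confidence intervals, as section 17.4.2 already plans for continuous measures.

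**Cost.** Seven visits × 16 subjects = 112 assays if all complete, or 6 × 16 = 96 if V10 is not a laboratory visit, plus any discontinuation samples. A leaner version with V5, V8 and V12 needs 3 × 16 = 48 and would still give a baseline and two on-treatment values. No visit or venepuncture is added. The change is a short edit in three places, but section 16.2 requires prior Institutional Review Board approval.

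**Separate point, not part of the argument above.** Urine hCG is also V0 only, although sirolimus can first be given at V5 and section 14.10.9 stops dosing at once in a pregnant subject. Contraception is required, but no test is planned before that first dose. Repeating hCG at V5, before dosing, in female subjects who could be pregnant would use urine already collected at that visit.

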### Thoracic Radiography

The principal investigator or subinvestigator will perform thoracic radiography during the screening phase (V0) to examine incidence of pulmonary interstitial opacity, and record the results on the electronic case report forms.

### Pure-tone Audiometry

The principal investigator or subinvestigator will perform pure-tone audiometry during the screening phase (V0), Phase I (V1, V3, and V4), Phase II (V5, V7, V8, V9, V10, V11, and V12), the follow-up phase (V13), and at discontinuation, and record the results on the electronic case report forms.

### Auditory Brainstem Response

The principal investigator or subinvestigator will perform an auditory brainstem response test during the screening phase (V0), Phase I (V4), and Phase II (V12), and record the results on the electronic case report forms.

### Posturography

The principal investigator or subinvestigator will perform posturography during the screening phase (V0), Phase I (V1, V3, and V4), Phase II (V5, V7, V8, V9, V10, V11, and V12), the follow-up phase (V13), and at discontinuation, and record the results on the electronic case report forms.

### Caloric Test

The principal investigator or subinvestigator will perform a caloric test during the screening phase (V0), Phase II (V5, V9, and V12), and at discontinuation, and record the results on the electronic case report forms.

### c-VEMP Test

The principal investigator or subinvestigator will perform a c-VEMP test during the screening phase (V0), Phase II (V5, V9, and V12), and at discontinuation, and record the results on the electronic case report forms.

### Speech Audiometry

The principal investigator or subinvestigator will perform speech audiometry during the screening phase (V0), Phase I, (V4), Phase II (V12), and at discontinuation, and record the results on the electronic case report forms.

## Blood Concentration of Sirolimus

The principal investigator or subinvestigator will collect blood for analysis of blood concentration of sirolimus during Phase II (V5, V6, V7, V8, V9, V10, V11, and V12). Analysis of the blood will be entrusted to an external contractor.

